## Protocol Amendments

### Summary of change(s) since last version of protocol

| SECTION                                                | DESCRIPTION OF CHANGE                                                                                                                                                                                                                                                                                                                                                                                                                   |
|--------------------------------------------------------|-----------------------------------------------------------------------------------------------------------------------------------------------------------------------------------------------------------------------------------------------------------------------------------------------------------------------------------------------------------------------------------------------------------------------------------------|
| Title page                                      | Version number and date                                                                                                                                                                                                                                                                                                                                                                                                                 |
| Appendix 4: Comfort of treatment questionnaire  | 
Descriptive introduction added: We would like to know how you felt whilst receiving your Rhenium treatment. In particular, any pain that may have been felt. Please note that pressure or discomfort do not constitute pain for the purpose of this question. Also please keep in mind if your pain is due to your lesions, rather than the treatment itself.
 
Question 1 clarified by adding wording 'prior to treatment'
 |
| Appendix 6: Guidance on bleeding post treatment | Guidance notes added for bleeding, post treatment                                                                                                                                                                                                                                                                                                                                                                                       |
| SOA                                             | Removal of permissible day rage for day 0:
Rhenium-SCT treatment                                                                                                                                                                                                                                                                                                                                                             |
| Number of subjects                              | Clarification of wording only: 25 Subjects are required per site. Approximately 210 subjects will be recruited (30 subjects per site, from 7 sites), to allow for screening failure or loss to long term follow up.                                                                                                                                                                                                                     |
| Exclusion criteria added                        | Participation in another clinical trial or administration of any investigational product or experimental product within 60 days or 5 half-lives (whichever is longer) prior to screening.                                                                                                                                                                                                                                               |

# 1. SYNOPSIS

## **Title of Study:**

Efficacy of Personalised Irradiation with Rhenium-Skin Cancer Therapy (SCT) for the treatment of non-melanoma skin cancer; a phase IV multi-centre, international, open label, single arm study.

## **Rationale:**

Non-melanoma skin cancer (NMSC), also known as keratinocyte cancer, includes basal cell carcinoma (BCC) squamous cell carcinoma (SCC) and various other less common lesions. NMSC is the most common form of cancer in humans. The most common cause of NMSC is sun exposure, while other predisposing factors include genetic skin conditions and immunosuppressive diseases or treatments. Although a range of definitive treatment options is currently available, these are subject to various limitations of effectiveness, safety, tolerability, and acceptability. New, non-invasive, non-scarring treatment options that can be delivered quickly in an outpatient setting would represent a significant improvement in the standard of care.

Rhenium-SCT is a novel form of brachytherapy for NMSC, which uses the Beta emitter radioisotope Rhenium-SCT. During treatment, the affected area of the skin is covered with a sterile protective foil. Rhenium-SCT is then applied in a matrix on the foil using a special applicator device. The irradiation time required to achieve the desired target dose (50Gy) at the defined penetration depth is calculated based on the radioactivity of the substance being applied and the surface area to be treated. At the conclusion of the calculated irradiation time, the matrix is removed by pulling the foil from the skin. The procedure is highly effective, while also non-invasive, and non-scarring. It can be provided without anaesthesia, over a short period of time and in an outpatient setting. As such, the service offers multiple practical, economic, and subject relevant benefits over existing management options, especially surgical removal of larger lesions. It is expected that treatment with Rhenium-SCT Brachytherapy will have a positive impact on the quality of life of subjects being treated. The reduced scarring and healing time mean subjects can return to their normal lifestyle sooner than would be expected for a surgical treatment.

Rhenium-SCT brachytherapy offers a new modality for treating more serious presentations of NMSC, which is non-invasive, can usually be delivered in a single session, over a short period of time, without the need for anaesthesia, in an outpatient setting. It will be particularly beneficial for lesions which are difficult to treat surgically, due to their size and or location (e.g., ears, nose, eyelids, shins, collarbone).

Clinical trials have shown the procedure to deliver remission rates similar those reported for either conventional or Mohs surgery, without functional mutilation or scarring and associated requirement for corrective or cosmetic repair. The net impact of these benefits for subjects, in terms anaesthesia and infection risk, procedural and post-operative pain, disfiguration and scarring, health related quality of life, healthcare costs, and functional and economic wellbeing are very significant. With this in mind, further clinical trials to demonstrate the ongoing benefit in terms of response rates, will offer efficacy and long-term data, as well as important subject reported outcome measures.

Rhenium-SCT has benefit in patients who are not suitable for surgery, perhaps because of comorbidities or tumour location. In addition, treatment with Rhenium-SCT has benefit as a single treatment and would be favourable for patients for whom several sessions of Radiation Therapy may not be appropriate or acceptable.

**Registration Status:**

EC Certification – Registered

ISO 13485:2016 – Registered

TGA – Currently undergoing conformity Assessment – In progress

**Phase of development:**

Phase IV study/ Post Marketing Clinical Follow-up (PMCF)

**Classification:**

**Base Station and Applicator**

The Rhenium-SCT application system, constituted by the Base Station and the Applicator, can be classified as a class I device as per the Medical Device Regulation (MDR) Annex VIII Rule 1.

Base Station REF: 0200

Applicator REF: 0100

**Measurement Station**

According to the classification rules set out in EU MDR (EU 2017/745), MST is a Class IIb device.

Measurement Station REF: 0401 or 0404

**Carpoules filled with radioactive compound (Re-188 compound)**

According to the Medical Device Regulation Annex VIII classification rule 9, paragraph 3, the OncoBeta Rhenium-188 compound can be classified as a medical device class IIb.

Radioactive carpoules REF: 0300

Please note that we do not specify the model and/or type directly, but this is linked with the reference number and the serial numbers that we give to the different stations/devices.

**Protective Foil**

The foil is a 3rd party product and it is a medical device classified as class Is.

**Model / Type:**

Oncobeta Rhenium-SCT

**Subject Population:**

Subjects with stage I or II NMSC (histologically confirmed BCC or SCC [SCC Well to Moderately differentiated])

**Studied duration (planned):**

12 months, with 24 months long-term follow-up

**Number of subjects (planned):**

**Number of sites:**

7 sites in total: Australia (4 sites) and Europe: (Germany, Austria and UK 1 site each)

25 Subjects are required per site. Approximately 210 subjects will be recruited (30 subjects per site, from 7 sites), to allow for screening failure or loss to long term follow up.

**Type of study, study design:**

Prospective, multicentre, single arm, open-label, phase IV study/ Post Marketing Clinical Follow-up (PMCF) study.

An interim analysis is planned once 50% of overall (total) subjects have been treated and have had a 6 month follow up visit.

**Study objectives:**

**Primary objective:**

- To assess the proportion of lesions achieving complete response (CR) as per MODIFIED VISUAL RECIST criteria

**Secondary objectives:**

- To assess change from baseline in Quality of Life (QoL)
- To assess treatment comfort
- To assess cosmetic outcomes

**Primary endpoint:**

- The number and percentage of lesions achieving CR during the study

**Secondary endpoints:**

- Adjusted mean change from baseline in QoL score at each timepoint
- Frequency and percentage of subjects reporting each option on the treatment comfort questionnaire
- Adjusted mean cosmetic outcome score.

**Safety endpoint:**

- Adverse events by severity and by relationship to Rhenium-SCT, including radiation dermatitis, dry skin, skin ulceration, alopecia, skin induration, hypo/hyperpigmentation, and telangiectasia.

**Criteria for inclusion:**

1. Stage I or II BCC or SCC (SCC Well to Moderately Differentiated), and clinically node negative disease
2. Confirmed Histology, and with depth of lesion noted
3. Subjects with up to 3 lesions suitable to enter the study (subjects with more than 3 lesions are not excluded from the study, however 3 target lesions are determined for study evaluation only.)
4. Subjects able and willing to comply with the requirements of the study
5. Age  $\geq 18$  years
6. Informed Consent signed by the subject consenting to undergo the study
7. Lesions up to 8cm^2
8. Lesions with a depth up to 3mm confirmed on biopsy report AND deemed appropriate clinically by treating clinician
9. Subjects who are not deemed suitable for surgery, for example due to tumour location, performance status or other comorbidities as deemed relevant by the treating clinician
10. Patients who may have declined Surgery and/or fractionated Radiation Therapy

**Criteria for exclusion:**

1. Inability to personally provide written informed consent or to understand and collaborate throughout the study
2. Inability or unwillingness to comply with study requirements
3. Prior treatment with surgery or radiation therapy for their target lesion(s)
4. Depth of lesion greater than 3mm as defined by Biopsy and/or clinical assessment
5. Lupus and Scleroderma
6. Basal cell naevus syndrome, xeroderma, vitiligo and albinism
7. Prior laser at the tumour site
8. Malignant melanoma systemic therapy ongoing
9. Any ongoing treatment for malignancy, or in the last 4 weeks prior to study entry
10. A tumour affecting nerves or bony structures
11. Clinical concern of metastatic disease
12. Pregnancy and/or Lactation
13. Pathological exclusions: Perineural Invasion, Lymphovascular invasion
14. Anatomical exclusions: NMSC's of the Medial canthus, eyelid margin (upper and lower), Vermillion lip
15. Participation in another clinical trial or administration of any investigational product or experimental product within 60 days prior to screening.

**Investigational Device:**

Rhenium-SCT

**Treatments, dose, mode of administration, duration of treatment:**

Rhenium-SCT (50Gy dose at target depth) will be administered on Day 0, as a single treatment, by application on a protective foil applied over the area to be treated, such that the radioactive material does not come into contact with the subject. The depth of lesion is determined before treatment by Histology (biopsy).

The lesion is marked out prior to treatment with a 5mm safety margin. The irradiation time required to achieve the desired target dose at the defined penetration depth is calculated based on the amount of radioactivity of the substance being applied, the surface area to be treated and the depth of the lesion. The dose at target depth, the deepest point of the lesion, is defined as 50 Gy. This dose, also known as target dose, ensures the mortality of all tumorous cells at the target depth. After the calculated irradiation time has elapsed, the Rhenium-SCT is removed by pulling the foil from the skin. A full user guide will be provided to the site.

Criteria for evaluation:

**Efficacy:**

1. Rate of complete response (CR) for subjects treated with Rhenium-SCT at 12 months after treatment

MODIFIED VISUAL RECIST (adapted from Response Evaluation Criteria in Solid Tumours) CRITERIA 1.1

- Complete response (CR): disappearance of the target lesion/s
  - Partial Response (PR):  $\geq 30\%$  reduction of the larger initial diameter of the target lesion or sum of the larger initial diameters of the target lesions
  - Progressive Disease (PD):  $\geq 20\%$  increase in the largest initial diameter of the lesion or sum of the larger initial diameters of the target lesions
  - Stable Disease (SD): Neither partial response or progressive disease
2. Quality of Life (Baseline: prior to therapy, 6 months after therapy, and 12 months after therapy) – NMSC QOL questionnaire
  3. Overall response rate (ORR)
  4. Comfort of treatment with Rhenium-SCT using short questionnaire
  5. Cosmetic outcome (measured 12 months after therapy) using VAS. Both subject and clinician assessed.

**Safety**

Common Terminology Criteria for Adverse Events (CTCAE) 5.0 grading for acute and late effects, relevant to treatment:

- Radiation dermatitis
- Skin ulceration
- Alopecia
- Skin induration
- Hypo/hyperpigmentation

- Telangiectasia

### **Statistical methods:**

#### **Sample size calculation:**

The primary objective of the study is to estimate CR rate and show non-inferiority to historical values for CR rate following surgery and or radiotherapy. CR rate for BCC is 91% at 5 years and for SCC 79%. Review of the published papers for brachytherapy shows the split between BCC and SCC is 2:1, 1.68:1 and 2.1:1.

Based on previous studies, the CR rate for BCC and SCC is expected to be close to 100% following Rhenium-SCT treatment. For simplicity, assuming 1 lesion per subject, a sample size of 120 subjects is sufficient to provide at least 80% power to conclude non-inferiority using a one-sided alpha of 0.025 under the following circumstances (Table 1).

In this study, approximately 210 subjects will be recruited to allow for screening failure or loss to long-term follow-up) and ensure a minimum of 120 patients are included in the analysis.

**Table 1. Sample size calculation**

| Non-inferiority margin | Assumed CR rate |
|-------------------------------|------------------------|
| 85%                           | ≥94%                   |
| 86%                           | ≥94%                   |
| 87%                           | ≥95%                   |
| 88%                           | ≥96%                   |
| 89%                           | ≥97%                   |
| 90%                           | ≥97%                   |

CR: Complete response

### **Analysis Populations**

#### **Intent-to-Treat (ITT) Population**

The ITT Population is defined as all subjects who were enrolled into the study, received treatment and have at least one post baseline value for efficacy data.

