### **9.1.1 Informed Consent Visit / Screening and baseline (Day -30 to Day -1)**

The subject will be fully informed of all study procedures and implications both verbally and in writing via use of an informed consent form. Once a subject has signed the informed consent form, a subject number (identifier) will be assigned.

Within 30 days prior to the administration of the first dose of study medication, the following procedures and assessments must be completed, and all inclusion and exclusion criteria must be met.

- Obtain informed consent
- Check of inclusion and exclusion criteria, including confirmation of BCC or SCC via histology AND confirmed by clinician review
- Target lesion(s) dimensions including depth of lesion
- Demographic data
- Baseline Modified Visual RECIST (dimensions only)
- QoL Questionnaire (via App or via eCRF or paper for subjects with no phone)
- Medical history
- Relevant concomitant medication
- Photographs of lesions to be treated are taken at the site and uploaded to the eCRF (if a medical photographer is available this is preferable)

The investigator will review all information obtained from the screening procedures. Screening failures, i.e., screened subjects not in compliance with all criteria, are to be excluded and the reason will be recorded. Subjects who fulfil all the inclusion criteria and none of the exclusion criteria will be eligible to participate in the study. Information of subject's study participation can be provided to the subject's general practitioner upon request, provided the subject has given consent for this to occur and this consent is documented in the source notes accordingly.

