### **11.4.2 Full Analysis Set**

The full analysis set (FAS) comprises all subjects who provided consent and were enrolled in the study.

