#### **Intent to Treat Set**

The intent to treat (ITT) set comprises all subjects in the FAS who received treatment and for whom at least one item of efficacy data is available.

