### **Secondary efficacy endpoints: Change from baseline in QoL, comfort of treatment, and cosmetic outcomes**

The QoL questionnaire will be scored according to the author's instructions. Change from baseline in score will be calculated. Descriptive statistics will be presented for actual score and change from baseline by timepoint, overall and by tumour type (BCC/SCC). A mixed model will be fitted with change from baseline as the outcome variable. Baseline score will be included as a covariate and timepoint (6 months/12 months) tumour type, tumour stage as factors. Other relevant prognostic factors assessed at baseline will be included. Subject will be included as a repeated term to acknowledge the data structure. From the model the adjusted mean change at each timepoint will be obtained and presented with 95% confidence limits. Adjusted mean change will be estimated overall and by tumour type.

Comfort with treatment is being assessed using a short questionnaire. The frequency (and percentage) of subjects reporting each option for each question will be presented.

Cosmetic outcome (subject and clinician) is being assessed at two timepoints (12 months and 24 months respectively) using a Visual Analogue Scale (VAS). Descriptive statistics will be presented overall and by tumour type (BCC or SCC). A mixed model will be fitted with VAS as the outcome variable. Tumour type and tumour stage will be included as factors. Other relevant prognostic factors assessed at Baseline will be included. From the model the adjusted mean score will be obtained and presented with 95% confidence limits. Adjusted mean score will be estimated overall and by tumour type.

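### The ITT set has two definitions that differ for treated subjects with no post-baseline efficacy data, and neither settles how lesions without a response reading enter the primary CR percentage

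*Protocol*

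**What the plan says.** **Two ITT definitions.** The synopsis (Analysis Populations) requires enrolment and that subjects "received treatment and have at least one post baseline value for efficacy data". Section 11.4.2, under Intent to Treat Set, takes "all subjects in the FAS who received treatment and for whom at least one item of efficacy data is available". The parent set there, the FAS, is "all subjects who provided consent and were enrolled in the study".

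**What counts as efficacy data, and when it is collected.**
- Before treatment, Section 9.1.1 requires "Baseline Modified Visual RECIST (dimensions only") and the QoL questionnaire. The synopsis lists QoL among its efficacy criteria with its baseline reading: "Quality of Life (Baseline: prior to therapy, 6 months after therapy, and 12 months after therapy").
- By day 14, the comfort questionnaire is answered (Sections 9.1.2.2 and 9.2.2). The synopsis efficacy criteria include "Comfort of treatment with Rhenium-SCT using short questionnaire", and Section 11.7 has the heading "Secondary efficacy endpoints: Change from baseline in QoL, comfort of treatment, and cosmetic outcomes".
- At 6 months, the first post-baseline Modified Visual RECIST reading is taken (Table 2, Section 9.1.3).

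**Analysis and missing data.** The synopsis efficacy analysis and Section 11.7 present the percentage of lesions in CR with exact 95% limits; neither names an analysis set. Section 11.11 uses available data for all efficacy assessments and rules out imputation.

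**Leaving the study.** Subjects who need further or other treatment for a target lesion leave (Sections 6.1, 7.3.1 and 9.1.4). A final examination is requested where it can be arranged (Sections 7.3.1 and 9.1.4).

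**Safety set.** The synopsis draws the Safety Population from the ITT set. Section 11.4.1 takes all treated subjects with safety data.

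**The concern.** One label, ITT, carries two membership rules. Baseline lesion dimensions and baseline QoL satisfy the rule in Section 11.4.2 but not the one in the synopsis. A treated subject with nothing recorded after baseline is therefore ITT in one place and not in the other, and through the synopsis Safety Population the same subject can be lost from a safety set as well.

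Behind this lies a gap common to both rules. The primary result is a proportion of lesions, and its denominator is not fixed. Neither rule asks for a response reading, so a subject can be in the ITT set with a treated lesion that was never read. No set is named for the CR percentage, and the available-data rule allows that lesion to be left out.

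This matters because a reading can be missing for reasons linked to outcome: a subject who needs other treatment for the lesion leaves the study. Leaving such lesions out can raise the CR percentage in a single-arm trial that compares it with a fixed threshold.

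**Working it through.** **Step 1. Who is in which set.** Take treated subjects, all with the required baseline data, and vary the last item they supply.

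| Last efficacy item supplied | Synopsis ITT | Section 11.4.2 ITT | Response reading |
|---|---|---|---|
| Baseline only | out | in | none |
| Day-14 comfort answer, nothing later | in | in | none |
| 6-month visit or later, with RECIST | in | in | yes |

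Only the first row separates the definitions. The second row shows that both admit subjects with no response reading.

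**Step 2. What happens to an unread lesion.** It has no CR, PR, SD or PD category. If Section 11.11 is read as leaving it out, the CR percentage is the same under either ITT definition. If it is counted as not CR, it stays in the denominator whenever its subject is in the set. The protocol does not state the second rule, and names no set to which it would apply.

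**Step 3. The plan's own figure.** Section 11.1 states at least 80% power with 120 subjects at one-sided alpha 0.025 for six pairs of threshold and assumed CR rate. I took the smallest r with P(X ≥ r | n = 120, threshold) ≤ 0.025, then computed P(X ≥ r | assumed rate). Exact power for 85/94, 86/94, 87/95, 88/96, 89/97 and 90/97 is 89.3%, 81.6%, 85.3%, 89.1%, 93.0% and 84.7%. The stated figure reproduces, and the ITT wording does not change it.

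**Step 4. Sensitivity to the counting rule (illustration, not the effect of the definitional mismatch).**
- Assumptions: 120 read lesions, one per subject, and m further treated lesions with no reading, counted as not CR.
- Lower limit (Clopper-Pearson): L = 0.025 quantile of Beta(x, n − x + 1), with x lesions in CR and n = 120 + m.
- The CR counts and m are assumed; the thresholds are three of the six in Table 3.

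| CR among 120 read | Threshold | m = 0 | m = 1 | m = 2 | m = 3 |
|---|---|---|---|---|---|
| 113 (94.2%) | 86% | 88.4% | 87.4% | 86.5% | 85.6% |
| 115 (95.8%) | 88% | 90.5% | 89.5% | 88.5% | 87.6% |
| 116 (96.7%) | 90% | 91.7% | 90.6% | 89.6% | 88.6% |

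For the middle row the point estimates are 115/120 = 95.8%, 115/122 = 94.3% and 115/123 = 93.5%. With two unread lesions the lower limit is still above 88%; with three it is below. In the other rows the threshold is crossed at three (86%) and at two (90%). If unread lesions are left out, every row stays at its m = 0 value.

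**The case against.** The strongest reply is that this is a wording slip with no demonstrated effect on the result. Four parts of it deserve an answer.

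- **The affected group is small.** A reader might infer that everyone lost before the 6-month reading falls into one ITT set only. The documents do not support that: a subject who answers the comfort questionnaire by day 14 has a post-baseline efficacy value and is in both sets. This stands, and the point is limited accordingly.
- **The CR percentage need not differ.** A reader might also infer that analysts following the two sections must report different CR rates. They need not: if unread lesions are dropped as unavailable, the rates agree. This stands too, but it shows that the denominator is open, not that it is settled.
- **Early leavers may still be read.** Sections 7.3.1 and 9.1.4 ask for a final examination. If that means the visit Table 2 labels as 12 months and end of study, it includes Modified Visual RECIST. This would reduce the number of unread lesions. It is requested only where possible, however, and the visit is called end of treatment, a label Table 2 does not use.
- **The SAP can settle it.** Naming the analysis set is often left to the SAP. But the protocol gives two ITT rules itself and fixes the missing-data rule in Section 11.11. A SAP would have to choose between conflicting protocol texts, and could not count unread lesions as not CR without departing from that section.

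**Conclusion.** The inconsistency is real. The two ITT definitions differ for treated subjects who have baseline but no post-baseline efficacy data, and only for them. Their number cannot be derived from the protocol. The gap between 210 recruited and 120 analysed (210 − 120 = 90) should not be cited as its size, because that allowance covers screening failures, who are never treated, and loss to long-term follow-up.

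The more consequential weakness is that neither definition, nor the CR analysis, says how a treated lesion without a response reading is counted, while the available-data rule lets it disappear. That can favour the device; the documents do not show that it will. In the illustrated cases two or three unread lesions beyond 120 read ones take the exact lower limit below the threshold. This rests on assumed CR counts near the tabulated rates, one lesion per subject, and unread lesions counted as not CR. A result further above its threshold would withstand more. The sample size statement is unaffected. The change should be made, as it is cheap and closes the question before data are seen.

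**What to change.** 1. Use one ITT definition in the synopsis and Section 11.4.2: all enrolled subjects who received Rhenium-SCT, with no requirement for efficacy data.
2. Name that set, in the synopsis efficacy analysis and in Section 11.7, as the set for the primary CR percentage, with every treated target lesion in the denominator.
3. State that a treated target lesion with no post-baseline response reading counts as not CR, and amend Section 11.11 to allow this. Without that amendment the new rule would contradict the ban on imputation.
4. Report the CR percentage among lesions with a reading as a sensitivity analysis.
5. Align the synopsis Safety Population with Section 11.4.1, so that treated subjects with safety data are not lost for want of efficacy data.

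The cost is wording in the synopsis and in Sections 11.4.2, 11.7 and 11.11, plus one row in the response table. No new data are needed. The drawback is a slightly less favourable CR figure whenever some treated lesions are never read.
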